### Secondary outcomes

Cardiopulmonary function consists of static lung function and cardiac function. Static lung function will be measured using the cardiopulmonary function instruments (JAEGER, Germany, product type: OXYCON PRO PC) by the professional operators at the Affiliated Rehabilitation Hospital of Fujian University of Traditional Chinese Medicine. Cardiac function will be measured using the Color Doppler ultrasound imaging device (product type: SIEMENS Acuson X300) by the professional operators at the medical examination center of Second People’s Hospital of Fujian Province.

Motor function includes lumbar and lower limb proprioception function and balance function. Lumbar and lower limb proprioception function will be measured using the Pro*-K*in proprioception evaluation and training system (produced by Tecnobody S.r.l, Dalmine, Italy, product type: PK254P) by the professional operators at the Affiliated Rehabilitation Hospital, Fujian University of Traditional Chinese Medicine. Balance control will be measured using the Pro*-K*in proprioception evaluation and training system (produced by Tecnobody S.r.l, Dalmine, Italy, product type: PK254P) by the professional operators at the Affiliated Rehabilitation Hospital, Fujian University of Traditional Chinese Medicine.

Physical parameters include body mass index (BMI, weight(kg)/height(m)^2^), waist-to-hip ratio (waist circumference (cm)/hip circumference (cm)), and flexibility. BMI will be measured using body scale by the assessors in this trial. Waist-to-hip ratio will be measured using a metric rule by the assessors in this trial. Flexibility will be measured through ‘sit and reach’ test using a ‘sit and reach’ tester produced by Zhongtitongfang Co., Ltd., Beijing*,* China (product type: CSTF-TQ-5000) by the assessors in this trial.

Blood lipid index consists of serum total cholesterol (TC), serum triglyceride (TG), low- density lipoprotein (LDL) and high-density lipoprotein (HDL). They will be measured by the operators at the Affiliated Rehabilitation Hospital, Fujian University of Traditional Chinese Medicine.

Fasting plasma glucose (FPG) will be measured by the operators at The Affiliated Rehabilitation Hospital, Fujian University of Traditional Chinese Medicine.

Inflammation factors including serum homocysteine (Hcy), serum c-reactive protein, IL-6, and TNF-α will be measured using the ELISA method by the assessors at Center Medical Laboratory, Fujian University of Traditional Chinese Medicine.

Quality of sleep will be measured through use of the Pittsburgh Sleep Quality Index (PSQI) [40]. The PSQI is a self-rated questionnaire which assesses sleep quality within a one month timeframe. Nineteen individual items generate seven dimensions: subjective sleep quality, sleep latency, sleep duration, habitual sleep efficiency, sleep disturbances, use of sleeping medication, and daytime dysfunction [41]. The Chinese version of PSQI has been reported by Liu Xianchen and his colleagues [42] to have acceptable internal consistency, test-retest reliability, construct validity, and criterion-related validity.

Quality of life will be measured through use of the Medical Outcomes Study (MOS) item short form health survey, SF-36 [43]. The SF-36 scale was constructed to survey health status in the MOS. The SF-36 includes one multi-item scale that assesses eight health concepts: limitation in physical activities because of health problems; limitations in social activities because of physical or emotional problems; limitations in usual role activities because of physical health problems; bodily pain; general mental health; limitation in usual role activities because of emotional problems; vitality; and general health perceptions [44]. The Chinese version of SF-36 has been reported by Jin Wen-zheng and his colleagues [45] to have reliability including split-half reliability, internal consistency, criterion validity and structure validity.

Happiness will be measured by use of the Memorial University of Newfoundland Scale of Happiness (MUNSH) [46]. The Chinese version of MUNSH has been reported by Wang Wen-Xin and his colleagues [47] to have better effect of re-measure of measuring table, intrinsic correlation by Hotelling’s *t*-test, better reliability in homogeneity and better reliability.

Emotion and mood will be measured through use of the Brief Profile of Mood State (BPOMS) [48]. The BPOMS is proven to be an excellent measure of affective mood state fluctuation in a wide variety of populations with a stronger reliability and validity. Six factors assessed identifiable mood or affective states include tension-anxiety, vigor-activity, depression-dejection, fatigue-inertia, anger-hostility, and confusion-bewilderment [49]. The Chinese version of BPOMS has been reported by Song Chi and his colleagues [50] to have acceptable internal consistency, construct validity, and criterion-related validity.

Self-confidence and self-esteem will be measured by use of the Rosenberg Self-Esteem Scale (RSES) [51]. The RSES is a self-esteem measure widely used in social-science research. The ten items, five of the items having positively worded statements and five having negatively worded ones, assess the subject’s level of self-esteem by asking the respondents to reflect on their current feelings [52]. The Chinese version of RSES has been reported by Xiangdong Wang and his colleagues [53] to have acceptable internal consistency, construct validity, and criterion-related validity.

### Safety

Although no adverse event from *Baduanjin* exercise is reported to this day, all unexpected adverse events during the intervention period will be reported to the project manager, and the causality with *Baduanjin* exercise intervention will be analyzed. If serious adverse events do occur, they will be reported to the primary researchers and ethics committee immediately and they will decide whether the participant needs to withdraw from this trial.

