## Methods/Design

This is a two-arm, randomized, assessor blinded, parallel controlled trial. The primary aim is to assess the effect of *Baduanjin* exercise on risk factors for stroke in the community elder population.

This trial will be performed at Wufeng Community Center, in Gulou District, Fuzhou City, China. A total of 170 eligible participants will be randomly allocated into intervention group (the *Baduanjin* exercise group) and control group (general physical activity group) in a 1:1 ratio. The participants in the intervention group will accept a 12-week *Baduanjin* exercise training, at the same time the others in the control group will maintain their original physical activity. Primary and secondary outcomes will be measured at baseline, end of 12-week intervention and after an additional 12-week follow-up period by the assessors who are not involved in this trial at the Affiliated Rehabilitation Hospital, Fujian University of Traditional Chinese Medicine. The statistic analysis will be performed by a statistician at the Center of Evidence Based Medicine, Fujian University of Traditional Chinese Medicine. A flow diagram of this trial is shown in Figure 1.

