### Follow-up

After the 12-week intervention period, all participants will enter an additional 12-week unsupervised follow-up period. They will resume their original lifestyle in the follow-up period, but they will be required to record their activity log as in the intervention period. Two supervisors will investigate the quality of each activity log by telephone once every two weeks.

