### Outcome assessment

The outcome assessment will be conducted at baseline (-2 to -1 weeks), end of intervention (13 weeks), and end of follow-up period (25 weeks).

The variables in this trial consist of basic characteristic variables, primary outcomes, and secondary outcomes. The basic characteristic variables will be measured at baseline (before randomized allocation); the primary or second outcomes will be measured at baseline, end of intervention period, and end of follow-up period, respectively. All outcome assessment will be independently performed by the assessors or operators who are blinded the allocation results of participants. A summary of all measurements in this trial is shown in Table 1.

**Table 1 T1:** Study flow chart

**Items**		**Before enrollment (weeks)**	**Intervention period (weeks)**	**End of the exercise (weeks)**	**Follow-up (weeks)**	**End of the follow-up (weeks)**
		**−2 to (-1)**	**1 to 12**	**13**	**13 to 24**	**25**
Recruitment		×				
Enrollment		×				
Inclusion criteria		×				
Exclusion criteria		×				
Informed consent		×				
Basic characteristic variables		×				
Randomization and allocation concealment		×				
Primary outcomes	Cerebrovascular function	×		×		×
	Cardiopulmonary function	**×**		**×**		**×**
Secondary outcomes	Motor function	**×**		**×**		**×**
	Physical parameters	**×**		**×**		**×**
	Blood lipids	**×**		**×**		**×**
	Fasting plasma glucose(FPG)	**×**		**×**		**×**
	Inflammation factors	**×**		**×**		**×**
	Quality of sleep	**×**		**×**		**×**
	Quality of life	**×**		**×**		**×**
	Happiness	**×**		**×**		**×**
	Emotion and mood	**×**		**×**		**×**
	Self-confidence and self-esteem	**×**		**×**		**×**
Adverse events recorded			×		×	
Activity log			×		×	

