### Statistical analysis

Statistical analyses will be performed using SPSS 21.0 (IBM, Chicago, IL, USA) software packages by a statistician, who is not involved in the outcome measurements, at Center of Evidence Based medicine, Fujian University of Traditional Chinese Medicine. The statistical significance is defined as two-sided *P* value of < 0.05. In descriptive analysis of the sample, the central tendency for the continuous variables will be expressed using mean (standard deviation) or median (interquartile range) for symmetrical distributions; normality will be tested using the Kolmogorov-Smirnov test. Appropriate transformations will be applied in cases of a non-normal distribution. The categorical variables will be expressed as proportions with their standard error. Statistical comparisons for the baseline characteristics, primary and secondary outcomes between groups will be compared using the Student’s *t-*test or Mann-Whitney *U*-test for continuous variables and the Pearson Chi-squared or Fisher exact test for categorical variables. Analysis of the primary and secondary outcomes will be on the basis of the intention-to-treat (ITT) population and per-protocol (PP) population. The result of the ITT analysis will be compared with that of the PP analysis to determine whether the results are consistent. Every effort will be made to minimize missing data and drop-out or loss to follow-up during the study period. Missing data will be filled by Bayesian methods. If the amount of missing data for primary outcome or potential confounders is substantial (that is > 10%), multiple imputation methods will be considered to perform the statistic analysis. Linear models or linear regression will be applied for dependent continuous variables and logistic regression models for dependent categorical variables if incomparability of baseline characteristics between groups appears. Subgroup analysis stratified by participants’ sex will be used for the primary outcomes. Analysis of variance (ANOVA) will be used for the repeated measurement data, and the *post hoc* comparison will be applied if the difference is found to be significant. Adverse events will be listed and analyzed using a Chi-squared or Fisher’s exact test. Severe adverse events will be listed in detail.

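### The Safety section, Table 1 and the analysis section give adverse events three different scopes, so the between-group safety comparison could be incomplete

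*Protocol article*

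**What the plan says.** Three places in the protocol article bear on adverse events.

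- **Safety.** The section notes that no adverse event of the exercise has been reported so far, and then says that "all unexpected adverse events during the intervention period will be reported to the project manager" and that causality with the exercise will be examined. A separate sentence deals with serious events: "If serious adverse events do occur, they will be reported to the primary researchers and ethics committee immediately".
- **Outcome assessment, Table 1.** The row "Adverse events recorded" is marked in two columns: the intervention period (weeks 1 to 12) and follow-up (weeks 13 to 24).
- **Statistical analysis.** "Adverse events will be listed and analyzed using a Chi-squared or Fisher" gives the test for the comparison. It names no period and no class of event. Severe events are also to be listed in detail.

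The two periods are of equal length. The Follow-up section says: "After the 12-week intervention period, all participants will enter an additional 12-week unsupervised follow-up period".

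**The concern.** The Safety section narrows the events in two ways, to unexpected ones and to the intervention period. Neither limit appears in Table 1 or in the analysis section. Study staff who take the Safety section as their instruction would not pass on an event in week 16, nor one in week 4 that they regarded as an ordinary result of exercising. Staff who work from Table 1 would record both.

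The limit by expectedness is the more awkward of the two. The article has no list of expected events, so each person must decide case by case before anything is reported. Expectedness is better assigned after an event has been captured than used as a filter on capture.

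At stake is the count that enters the Chi-squared or Fisher test. The article describes the exercise as safe, and readers will look to this trial for evidence on that. A comparison built on an undefined set of events is weak support for such a statement.

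**Working it through.** The plan gives no figure on this point to reproduce. The check is a side-by-side reading, followed by one piece of arithmetic.

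**Scope by place**

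| Place in the article | Step it describes | Which events | Which weeks |
|---|---|---|---|
| Safety, first sentence | Report to project manager, causality review | Unexpected only | Intervention period (1 to 12) |
| Safety, second sentence | Report to primary researchers and ethics committee | Serious | No limit stated |
| Table 1 | Recording | Adverse events, no limit stated | 1 to 12 and 13 to 24 |
| Statistical analysis | Listing and between-group test | Adverse events, no limit stated | No limit stated |

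**Two ways to read them together**

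1. The Safety section decides what reaches the dataset. The test then lacks non-serious events judged to be expected, and all non-serious events in weeks 13 to 24.
2. Table 1 decides what reaches the dataset, and the Safety section covers escalation only. The test is then complete, but events in follow-up and events judged to be expected enter it without the causality review that the others receive.

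The text does not choose between these readings.

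**Size under reading 1**

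- Intervention: 12 weeks (Methods/Design). Follow-up: 12 weeks (Follow-up section).
- Share of scheduled observation outside the period named in the Safety section: 12 / (12 + 12) = 0.50.
- With 170 participants and no drop-out (an assumption): 170 × 24 / 52 = 78.5 person-years in all, of which 170 × 12 / 52 = 39.2 fall in follow-up.

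The number of events lost because they are judged expected cannot be calculated, since the article does not define the category.

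**Contact with each arm**

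In weeks 1 to 12 the exercise arm meets coaches on five days a week, up to 5 × 12 = 60 sessions. For controls, the article describes only the activity log in that period. In follow-up, the supervisors' two-weekly calls about the log cover both arms, about 12 / 2 = 6 calls each. The period named in the Safety section is thus the one in which the described contact differs most between arms. The article does not say that events are collected through these contacts, so this is a reason to define collection and not evidence of bias.

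**The case against.** The strongest reply is that the passages describe different steps and can coexist. The Safety section concerns escalation, Table 1 concerns recording, and the Statistical analysis section concerns the test. Escalating a subset for causality review while recording and analysing everything is a coherent system. This stands, and it means that omission is a possibility and not something the plan lays down.

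A second reply is that the Safety section starts from the premise that no adverse event of this exercise is known, so nearly any event would count as unexpected. This also stands in part: no event is documented as expected, and none is named as excluded. It does not settle the matter, because the exclusion criteria mention contraindications related to sports injury. The article therefore does foresee exercise injury, and a coach might reasonably treat a minor strain as expected. That example is mine and is not in the article.

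A third reply is that serious events are covered without limit. This is correct and confines the point to non-serious events.

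Finally, detailed collection procedures belong in a full protocol that is not shown. That is fair for procedures left out, but here the article states two scopes that differ.

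A reader might go further and infer that the safety comparison will omit follow-up events and all foreseeable exercise injuries, so that 39 person-years are lost. The documents do not support this. It requires the first reading above, which nothing in the text imposes.

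**Conclusion.** The inconsistency is real, and the passages need to be reconciled. The between-group comparison could omit non-serious events judged to be expected and non-serious events in the 12 follow-up weeks, which are half of the 24 scheduled weeks. If those events are included, they could enter the test without causality review. Serious adverse events are not limited in this way.

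The 50% share rests only on the stated durations. The 39.2 of 78.5 person-years also assumes 170 participants with no drop-out, and it counts as a loss only if the Safety section governs what is analysed. The primary outcome analysis is unaffected. The point is worth acting on because a stated rule filters events against the plan's own schedule and the correction is cheap.

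**What to change.** Reword the Safety section to agree with Table 1: all adverse events, whatever their expectedness, are recorded and reported in both arms over weeks 1 to 24, and expectedness, seriousness and relatedness are classified afterwards. Add a sentence to the Statistical analysis section saying that this full set enters the between-group comparison.

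Collect events in the same way in both arms. Both arms already keep the activity log in both periods, so an adverse event item can be added there. The same question can be added to the existing two-weekly calls in follow-up.

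The cost is a wording change, one item in the log, one question per call and slightly more data entry. According to the Trial status section recruitment has begun, so the change should be made promptly, to keep collection uniform for as many participants as possible.

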### Statistical analysis

Statistical analyses will be performed using SPSS 21.0 (IBM, Chicago, IL, USA) software packages by a statistician, who is not involved in the outcome measurements, at Center of Evidence Based medicine, Fujian University of Traditional Chinese Medicine. The statistical significance is defined as two-sided *P* value of < 0.05. In descriptive analysis of the sample, the central tendency for the continuous variables will be expressed using mean (standard deviation) or median (interquartile range) for symmetrical distributions; normality will be tested using the Kolmogorov-Smirnov test. Appropriate transformations will be applied in cases of a non-normal distribution. The categorical variables will be expressed as proportions with their standard error. Statistical comparisons for the baseline characteristics, primary and secondary outcomes between groups will be compared using the Student’s *t-*test or Mann-Whitney *U*-test for continuous variables and the Pearson Chi-squared or Fisher exact test for categorical variables. Analysis of the primary and secondary outcomes will be on the basis of the intention-to-treat (ITT) population and per-protocol (PP) population. The result of the ITT analysis will be compared with that of the PP analysis to determine whether the results are consistent. Every effort will be made to minimize missing data and drop-out or loss to follow-up during the study period. Missing data will be filled by Bayesian methods. If the amount of missing data for primary outcome or potential confounders is substantial (that is > 10%), multiple imputation methods will be considered to perform the statistic analysis. Linear models or linear regression will be applied for dependent continuous variables and logistic regression models for dependent categorical variables if incomparability of baseline characteristics between groups appears. Subgroup analysis stratified by participants’ sex will be used for the primary outcomes. Analysis of variance (ANOVA) will be used for the repeated measurement data, and the *post hoc* comparison will be applied if the difference is found to be significant. Adverse events will be listed and analyzed using a Chi-squared or Fisher’s exact test. Severe adverse events will be listed in detail.

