### Sample size

Sample size computation is based on the changes in cerebral vascular hemodynamic parameter between comparison groups with a 5% per comparison significance level and a two-tailed critical region. The mean and SD of cerebral vascular hemodynamic parameter in the control group as obtained from relevant literature are 32.0 and 6.0 respectively [37]. We expect a 10% mean improvement of this outcome after 12-week *Baduanjin* exercise intervention. A total of 170 participants is calculated as needed to detect the target effect size with 90% power. In order to avoid excessive loss to follow-up, we will illustrate in detail to the participants the potential health benefits of *Baduanjin* exercise. For completeness of whole trial progress we will also provide confidence incentives to participants. Furthermore, we will collect information from participants in both the *Baduanjin* exercise and the usual physical activity control group regarding the likelihood that they will drop out. This information will be used to attempt to reduce the incidence of drop-out.

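### Baseline adjustment depends on observed imbalance and no analysis is ranked first; a baseline-adjusted model fixed in advance is more precise and removes the choice

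*Protocol article*

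**What the plan says.** The Statistical analysis section of the protocol article contains three statements that bear on the same outcomes.

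- A between-group test: "Statistical comparisons for the baseline characteristics, primary and secondary outcomes between groups will be compared using the Student" t-test or the Mann-Whitney test for continuous variables. The same sentence tests the baseline characteristics between the arms.
- A conditional regression: linear models for continuous outcomes, and "logistic regression models for dependent categorical variables if incomparability of baseline characteristics between groups appears". The primary outcomes (flow velocities and the PI and RI indices, under Primary outcomes) are continuous, so the linear half of the sentence applies to them; it carries the same condition. No threshold and no list of covariates defines the condition.
- A repeated-measures analysis: "Analysis of variance (ANOVA) will be used for the repeated measurement data", with post hoc comparisons if it is significant.

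The section does not say which of these decides the primary outcome. Outcome assessment and its Table 1 schedule every primary and secondary outcome at baseline, week 13 and week 25. The Sample size section says: "Sample size computation is based on the changes in cerebral vascular hemodynamic parameter between comparison groups".

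**The concern.** In a properly randomised trial, a baseline difference between arms is a chance event. Testing for it says nothing about whether adjustment is worthwhile. What makes a covariate worth including is how well it predicts the outcome, and the best candidate is normally the outcome's own baseline value. The article measures that value in everyone, then uses it in a model only if an undefined imbalance turns up.

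Two things are at stake. The first is precision: the plan collects the information and in most trials would not use it. The second is freedom of choice. An undefined trigger, together with unranked analyses of one outcome, allows more than one P value for the same question. The A/B coding described under Blinding does not prevent this, because a small P value is visible without knowing which letter is which arm.

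**Working it through.** **Inputs from the article.** Sample size section: two-sided 5% level ("5% per comparison significance level and a two-tailed critical region"); control mean 32.0 and SD 6.0 ("The mean and SD of cerebral vascular hemodynamic parameter in the control group as obtained from relevant literature are 32.0 and 6.0 respectively"); effect 10% of 32.0 = 3.2 ("We expect a 10% mean improvement of this outcome after 12-week"). Arm size is 85 (Intervention section; 170 randomised 1:1).

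**Assumed.** The correlation r between the baseline and week-13 values is not given, so 0.3, 0.5 and 0.7 are used. The value 6.0 is taken as the SD of the outcome at one visit.

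**The plan's own figure.** The article states: "A total of 170 participants is calculated as needed to detect the target effect size with 90% power". From its inputs, n per arm = 2 × (1.960 + 1.282)² × 6.0² / 3.2² = 73.9, so 74 per arm and 148 in total (150 by the exact t calculation). With 85 per arm the unadjusted t-test has SE = 6.0 × √(2/85) = 0.920, noncentrality 3.2 / 0.920 = 3.48, and exact power 93.3%. The figure of 170 is therefore not reproduced without some unstated allowance. That is a separate matter and does not affect this point.

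**Step 1: gain from adjustment.** The ANCOVA residual SD is 6.0 × √(1 − r²), and error variance falls by the fraction r². The change-score SD is 6.0 × √(2(1 − r)). Power is from the noncentral t distribution at 85 per arm.

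| r (assumed) | ANCOVA SD | Variance cut | Power, unadjusted | Power, ANCOVA | Change-score SD | Power, change score |
|---|---|---|---|---|---|---|
| 0.3 | 5.72 | 9% | 93.3% | 95.2% | 7.10 | 83.2% |
| 0.5 | 5.20 | 25% | 93.3% | 97.9% | 6.00 | 93.3% |
| 0.7 | 4.28 | 49% | 93.3% | 99.8% | 4.65 | 99.4% |

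The standard error shrinks by the factor √(1 − r²), which is 0.954, 0.866 and 0.714. ANCOVA is at least as powerful as either alternative in every row.

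**Step 2: the conditional rule.** Read the trigger as P<0.05 for the baseline value of the outcome. Under randomisation it fires in about 5% of trials by construction. In simulation (85 per arm, 20,000 trials per setting), the rule of ANCOVA if triggered and t-test otherwise gave:

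- power of about 93 / 94 / 95% at r = 0.3 / 0.5 / 0.7, so nearly all of the ANCOVA gain is lost;
- type I error of about 4.9 / 4.4 / 3.6%, with a simulation error near 0.15 points (√(0.05 × 0.95 / 20,000)). The rule is slightly conservative, because it replaces the t-test in just those trials where chance baseline imbalance would most often make it falsely significant.

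**Step 3: free choice among analyses.** In the same simulation under no effect, reporting whichever of the t-test, ANCOVA and change score reached P<0.05 gave a type I error of about 9 to 10% across the three correlations. This is for one parameter at one visit. With two visits, the change-score test is the same as the group-by-time test of a repeated-measures ANOVA.

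**The case against.** The strongest reply is that an unadjusted comparison in a randomised trial is valid and, on the article's own inputs, already exceeds 90% power at 85 per arm. At r = 0.3 the gain is about 2 points. The article also condenses a fuller plan: the three methods may have distinct roles (visit-wise test, adjustment, time profile), and ranking them is commonly left to an analysis plan. Both points stand in part. They limit the severity, and the missing ranking alone would not be a finding. They do not rescue the stated rule, which an analysis plan would have to replace and could not merely complete.

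A reader might also infer more than the article supports:

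- *That the conditional rule inflates type I error.* Followed strictly, with the trigger read as in the check, it is conservative. Inflation arises only if someone picks among the analyses or decides after the fact what counts as imbalance.
- *That the trigger would fire in most trials.* With 15 to 20 independent baseline tests, 1 − 0.95^15 = 54% to 1 − 0.95^20 = 64% of trials would show at least one. But the article fixes neither the number of tests nor the threshold, and variables such as height and weight are not independent.
- *That the Kolmogorov-Smirnov test selects the outcome test.* It appears in the descriptive part and leads to transformations.
- *That the ANOVA relies on a group main effect diluted by the baseline visit.* The article does not say which ANOVA term is tested; group-by-time is as available a reading.
- *That the t-test cannot match a sample size based on changes.* The article does not say whether raw values or changes are tested. If changes, baseline is already used, though less efficiently than by ANCOVA.

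**Conclusion.** The point holds as a defect of method with a better alternative at almost no cost. It is not an error that makes the trial invalid or underpowered. The article ties adjustment to chance imbalance, without a definition, when the relevant covariate is measured in everyone. What this costs in power depends on the unreported correlation: about 2 points at r = 0.3, 5 at r = 0.5 and 6 to 7 at r = 0.7, from a base of 93.3%. At r near 0, ANCOVA neither gains nor materially loses. These figures rest on reading 6.0 as the single-visit SD, on normal data and on no dropout. The 9 to 10% type I error describes what the unranked wording permits, not what the investigators say they will do. The change should be made.

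**What to change.** Name one primary analysis for each continuous primary outcome, to be used whatever the observed balance: a linear model (ANCOVA) of the week-13 value on arm and the outcome's own baseline value, reporting the adjusted difference with its 95% CI. A mixed model over weeks 13 and 25 with baseline value, arm, visit and arm-by-visit, reading the arm contrast at week 13, is an equal alternative.

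Delete the significance tests of baseline characteristics and the imbalance condition; describe baseline by arm instead. Keep the t-test or Mann-Whitney test and the repeated-measures ANOVA, labelled as sensitivity or descriptive analyses.

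The cost is wording only. The baseline measurements are already scheduled, and no visit, measurement or participant is added. The Trial status section says recruitment had only started, so the change can be made and dated well before the allocation codes are released.
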